### Sample size calculation

Our planned primary intention-to-treat analysis will compare dCBT-I + TAU versus WLC + TAU for self-reported cognitive impairment (BC-CCI). A systematic review of the cognitive functioning and CBT-I literature shows a standardised mean difference of 0.42 at post-treatment for self-reported outcomes [15]. We will recruit and randomise 404 participants (202 participants/arm). This sample size will give 90% power to detect a minimum standardised effect size of 0.42 at 5% level of significance, accounting for 40% attrition.

#### Statistical analysis

In accordance with Consolidated Standards of Reporting Trials (CONSORT) guidelines, we will record and report all participant flow [43]. Descriptive statistics of recruitment, dropout, and completeness of interventions will be provided. The main efficacy analysis will be via intention-to-treat including all participants, with no planned interim analysis for efficacy or futility. Baseline characteristics will be presented by randomised group without formal statistical tests. We will test the primary hypothesis for between-group change in the primary outcome (BC-CCI) at 10 weeks using analysis of covariance with baseline outcome measure and treatment assignment as fixed effects, and apply standard regression diagnostics. The analysis will use statistical techniques for handling missing outcome data under a missing-at-random assumption. Secondary outcomes will be analysed using an analogous method. Analysis of all treatment effects will be undertaken after follow-up (week 24) assessments are completed. Additional exploratory analyses will assess whether age moderates treatment-related effects on cognitive functioning outcomes.

We will use modern causal inference methods to investigate the mediation hypothesis. If the efficacy analysis shows significant between-group differences in the ISI and sleep efficiency (based on PSQI items) at 10 weeks, then we will use parametric regression models to test for the indirect effect of ISI/sleep efficiency on primary and secondary cognitive outcomes at 24 weeks, and the residual direct effect of treatment on cognitive outcomes at 24 weeks. Since all the measures are continuous, the indirect effects are calculated by multiplying relevant pathways and bootstrapping is used to produce valid standard errors for the indirect effects. All analyses will adjust for baseline measures of the mediators (ISI/sleep efficiency), outcomes and putative measured confounders. Mediation analyses are potentially biased by measurement error in mediators and hidden confounding between mediators and outcomes and we will investigate the sensitivity of the estimates to these problems. All analyses will be carried out using Stata [44].

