## Methods/design

### Research design

The study is a parallel-group, superiority RCT of dCBT-I (+ TAU) versus WLC (+ TAU). The study will be carried out completely online. Participants will be administered screening, informed consent, assessments (tasks and questionnaires), allocation to condition, and intervention through web-based platforms. Online assessment of our primary and secondary dependent variables will take place at 0 (baseline), 10 (post-treatment), and 24 (follow-up) weeks. At week 25 all participants allocated to the WLC will be offered dCBT-I to improve their insomnia (see Fig. 1 for trial design). Ethical approval has been granted from the University of Oxford Medical Sciences Inter-Divisional Research Ethics Committee (R46116/RE001) and the trial is registered at ISRCTN (ISRCTN89237370).

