### Randomisation and allocation concealment

This study will use simple randomisation with an allocation ratio of 1:1, as recommended for large clinical trials [26]. Randomisation will be carried out using the randomisation function within Qualtrics Survey Software (Qualtrics, Provo, UT, USA). On completion of baseline measures, each subject will be randomly assigned by the software to either dCBT-I or WLC. The research team, therefore, will be unable to influence randomisation and will have no access to future allocations.

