### Assessment points

Assessments will take place at weeks 0 (baseline), 10 (post-treatment), and 24 (follow-up) (see Fig. 2). Participants are advised to allow enough time to complete the questionnaires and cognitive tasks in one session, on their home computer or laptop in a quiet, distraction-free environment. On completion of the trial (week 25), all participants in the control arm will be offered access to dCBT-I. Baseline variables include demographic information such as age, gender, ethnic group, partner status, employment status, and education. Frequency of sleep medication use will also be monitored at each assessment point.

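### Minor: the efficacy ANCOVA is valid, but adjusting also for age, education and baseline ISI would gain precision at almost no cost, mainly for the objective cognitive tasks

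*Protocol article*

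**What the plan says.** Under Statistical analysis, the protocol article tests the 10-week BC-CCI by "analysis of covariance with baseline outcome measure and treatment assignment as fixed effects". It then says: "Secondary outcomes will be analysed using an analogous method". Each efficacy model therefore holds two terms, the arm and that outcome's own baseline.

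Under Randomisation and allocation concealment: "This study will use simple randomisation with an allocation ratio of 1:1, as recommended for large clinical trials". No stratification or minimisation is described. The order of events is also given there: "On completion of baseline measures, each subject will be randomly assigned by the software to either dCBT-I or WLC".

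Under Assessment points: "Baseline variables include demographic information such as age, gender, ethnic group, partner status, employment status, and education". The ISI is a secondary measure, and under Research design: "Online assessment of our primary and secondary dependent variables will take place at 0 (baseline), 10 (post-treatment), and 24 (follow-up) weeks". Age, education and baseline ISI are thus in hand before the arm is known.

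In the efficacy analyses age appears only in an exploratory question, "whether age moderates treatment-related effects on cognitive functioning outcomes". The Background section reports that the objective impairments seen in insomnia go along with global insomnia severity.

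**The concern.** Covariates that predict the outcome beyond its own baseline reduce residual variance and so narrow the confidence interval for the arm difference. The article states the covariate set outright, so this is a choice it makes and not a detail left to the analysis plan.

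The choice matters most for the five objective tasks. The sample size statement concerns the BC-CCI only, and no power is stated for the tasks. Each task is brief and its baseline may be noisy, which would leave variance for age or education to explain. The trial admits anyone aged 25 or over and states no upper limit, so the age range may be wide. What is at stake is the width of the intervals on these secondary comparisons, not the validity of any test.

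**Working it through.** **Inputs from the protocol article.** Effect size 0.42, 90% power, 5% level, 40% attrition and 404 randomised (202 per arm), all from Sample size calculation. The model is as stated in Statistical analysis.

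**Assumptions (the article gives none of these).** Correlation between baseline and follow-up score: *r* for a task, *ρ* for the BC-CCI. Correlation *a* of age with the task score, taken as the same at both times. Share *q* of the variance left after baseline adjustment that the added covariates explain.

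**Step 1. Reproduce the sample size.** A two-sided two-sample t-test at effect size 0.42 needs 121 per arm (power 90.2%). 121 / 0.6 = 201.7, rounded up to 202 per arm, 404 in total. This matches exactly. It takes no credit for any covariate, so the planned baseline adjustment is already a bonus.

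**Step 2. Objective tasks: what age adds.** With baseline only, R² = *r*². With baseline and age, R² = (*r*² + *a*² − 2*ra*²) / (1 − *a*²). The cut in residual variance is *q* = 1 − (1 − R²) / (1 − *r*²).

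| *r* | *a* | R², baseline only | R² with age | Cut in residual variance |
|---|---|---|---|---|
| 0.6 | 0.3 | 0.360 | 0.376 | 2.5% |
| 0.4 | 0.4 | 0.160 | 0.229 | 8.2% |
| 0.3 | 0.5 | 0.090 | 0.253 | 18% |

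To put this in terms of power, take an illustrative task effect of 0.3, in units of the SD left after baseline adjustment (an assumption), with 121 completers per arm. Power is 64% without age. It rises to 65% with a 2.5% cut, 68% with an 8.2% cut and 73% with an 18% cut.

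**Step 3. Primary outcome.** No section says that age, education or ISI predicts the BC-CCI beyond its own baseline, so *q* is varied freely. Power is computed by the normal approximation with 121 per arm, effect 0.42 and SD √((1 − *ρ*²)(1 − *q*)).

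| *ρ* | *q* = 0 | 0.01 | 0.02 | 0.05 | 0.10 |
|---|---|---|---|---|---|
| 0.5 | 96.5% | 96.6% | 96.8% | 97.2% | 97.8% |
| 0.6 | 98.3% | 98.4% | 98.5% | 98.7% | 99.0% |
| 0.7 | 99.5% | 99.6% | 99.6% | 99.7% | 99.8% |

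At *ρ* = 0.5 the gain is 0.1 to 1.3 points. At higher *ρ* it is 0.7 points or less.

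**Step 4. The cost.** With 242 completers, three extra single-degree-of-freedom terms multiply the standard error by about √(238/235) = 1.0064. The break-even is *q* = 1 − 235/238 = 0.013. Below that there is no net gain, but even useless covariates widen the standard error by only 0.6%. Education entered as several categories would cost slightly more.

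**The case against.** The strongest reply is that nothing here is wrong. ANCOVA on the outcome's own baseline is valid under simple randomisation, it already contains the most obvious predictor, and the stated power does not depend on further covariates. All of that stands, and it is why the point is minor. It does not remove the gain in Step 2, which would cost only wording.

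A reader might infer four stronger claims. The document does not support them.

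- **Bias from imbalance.** The chance of a standardised difference above 0.2 on one covariate is 4.4% among 404 randomised (SD √(4/404) = 0.100) and 12% among 242 completers (SD √(4/242) = 0.129). The standard error and the 5% error rate already allow for this. It is not a bias.
- **A clear power gain for the primary outcome.** Starting from 90% ignores the baseline BC-CCI already in the model, and no variance cut for the BC-CCI can be sourced from the document.
- **A weak missing-at-random assumption.** The article names the assumption but does not limit the conditioning variables to arm and baseline score. The method may properly be left to the analysis plan.
- **A mismatch with the mediation models.** Those models need confounder adjustment because the mediator is not randomised. In linear models, extra baseline covariates leave the targeted mean difference between arms unchanged.

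Testing age as a moderator also does not show that age is prognostic. The age correlations in Step 2 remain assumptions.

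**Conclusion.** The point holds as a minor matter of efficiency. The planned model is sound, but it leaves unused covariates that are recorded before allocation.

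For the objective tasks, adding age would cut residual variance by 2.5% to 18% if *r* is 0.3 to 0.6 and *a* is 0.3 to 0.5, with age related equally to both scores. Education and ISI could add to this, but the document gives no figure for either. The Background's link between insomnia severity and objective impairment makes ISI a plausible predictor and no more than that.

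For the BC-CCI the gain cannot be sized from the document. At an assumed baseline correlation of 0.5 or more it is about 1 point of power or less over most of the range tried, and 1.3 points at the extreme. The 404 stands either way.

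**What to change.** Before any outcome data are seen, write the efficacy model as arm + baseline value of the outcome + age (continuous) + education + baseline ISI. Where the ISI is itself the outcome, its baseline enters once. Apply this at least to the five objective tasks and preferably to all outcomes, so that one model form serves throughout. Report the model with arm and baseline outcome only as a sensitivity analysis.

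The cost is a change of wording and a few degrees of freedom. No new data are needed, because the covariates are collected before allocation. The article reports recruitment as ongoing and places all treatment-effect analyses after week 24, so at that stage the change could still be prespecified. Made after results are seen, it would look data-driven.

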## Abstract

**Background:**

The daytime effects of insomnia pose a significant burden to patients and drive treatment seeking. In addition to subjective deficits, meta-analytic data show that patients experience reliable objective impairments across several cognitive domains. While Cognitive Behavioural Therapy for Insomnia (CBT-I) is an effective and scalable treatment, we know little about its impact upon cognitive function. Trials of CBT-I have typically used proxy measures for cognitive functioning, such as fatigue or work performance scales, and no study has assessed self-reported impairment in cognitive function as a primary outcome. Moreover, only a small number of studies have assessed objective cognitive performance, pre-to-post CBT-I, with mixed results. This study specifically aims to (1) investigate the impact of CBT-I on cognitive functioning, assessed through both self-reported impairment and objective performance measures, and (2) examine whether change in sleep mediates this impact.

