The aim of this study, therefore, is to investigate the impact of CBT-I on cognitive functioning, assessed through both self-report and objective measures. We will recruit participants meeting criteria for insomnia disorder who also endorse cognitive complaints, and conduct a parallel-group, randomised controlled trial (RCT) of CBT-I + TAU versus wait-list control (WLC + TAU). CBT-I will be delivered online via a website and/or app [20]. Online interventions have shown robust effects on insomnia severity and self-reported sleep parameters, with effect sizes in the range of face-to-face interventions [21, 22]. Assessments, including questionnaires and computerised cognitive tasks, will also be delivered and completed fully online. This will be the first examination of the impact of digital CBT-I (dCBT-I) on self-reported cognitive impairment and objective performance in participants meeting criteria for insomnia disorder.

The primary hypothesis for the trial is:dCBT-I will reduce self-reported cognitive impairment at the end of treatment (10 weeks) relative to WLC

The secondary hypotheses are:dCBT-I will reduce self-reported cognitive impairment at follow-up (24 weeks) relative to WLCdCBT-I will improve objective cognitive performance (in the following domains: simple attention, visual attention, episodic memory, working memory, and complex processing speed), relative to WLC (10 and 24 weeks)dCBT-I will reduce insomnia severity and improve sleep efficiency relative to WLC (10 and 24 weeks)Change in insomnia severity and sleep efficiency at week 10 will mediate change in self-reported cognitive impairment and objective cognitive performance at week 24dCBT-I will lead to improvements in fatigue, sleepiness, self-reported cognitive failures, depression, and anxiety relative to WLC (weeks 10 and 24)

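### The mediation analysis depends on week-10 significance of ISI and sleep efficiency, so an unconditional aim may go untested; the rule is ambiguous and selects on a path it then multiplies

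*Protocol article*

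**What the plan says.** The second paragraph of the Statistical analysis section opens the mediation plan with a condition: "If the efficacy analysis shows significant between-group differences in the ISI and sleep efficiency (based on PSQI items) at 10 weeks". It continues: "then we will use parametric regression models to test for the indirect effect of ISI/sleep efficiency on primary and secondary cognitive outcomes at 24 weeks". The residual direct effect falls under the same condition. Nothing is said about what happens if one or neither of the two sleep measures is significant.

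The estimator is a product of paths: "the indirect effects are calculated by multiplying relevant pathways and bootstrapping is used to produce valid standard errors for the indirect effects". The sensitivity work promised there concerns measurement error in the mediators and hidden confounding.

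Elsewhere the mediation question carries no condition. The Abstract gives it as aim 2, to "examine whether change in sleep mediates this impact", and its Methods/design part says that further analyses will establish the extent of mediation. The Background lists mediation by week-10 change in insomnia severity and sleep efficiency among the secondary hypotheses. The Discussion says that the study will settle the question.

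**The concern.** Three features of the condition are unsatisfactory.

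- **It can leave a stated aim without an analysis.** A p-value just above 0.05 at week 10 would stop the models that are meant to answer aim 2, and no fallback is given.
- **It can be read in two ways.** Joined by *and*, the two measures read as a joint requirement. A clear ISI effect with a narrow miss on sleep efficiency would then cancel mediation through ISI as well. The slash in *ISI/sleep efficiency* later in the sentence suggests that each mediator could instead be gated on its own result. If one measure passes and the other does not, the choice of reading decides whether anything is reported, and by then the results are known.
- **It selects on part of the estimate.** The indirect effect is the treatment-to-mediator path times the mediator-to-outcome path. Keeping only trials in which the first path is significant favours large estimates of that path. A bootstrap within a trial that passed does not undo this, and the planned sensitivity analyses do not address it.

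At stake is whether aim 2 is always answered, and whether a reported mediated effect is somewhat too large.

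**Working it through.** **The plan's own figure.** The Sample size calculation states: "This sample size will give 90% power to detect a minimum standardised effect size of 0.42 at 5% level of significance, accounting for 40% attrition". A two-sided two-sample t-test at 5% with 90% power and an effect of 0.42 SD needs 120.1, hence 121, per arm. Then 121 / 0.6 = 201.7, which rounds up to 202 per arm or 404 in total. The stated size reproduces. In reverse, 202 × 0.6 = 121 per arm is the analysed number under the planned attrition.

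**Inputs for the gate.**

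- Analysed per arm: 121 (planned 40% attrition) or 202 (none), from the protocol.
- Significance level: 5%, taken as two-sided because that reproduces the 404.
- Baseline-to-week-10 correlation of the mediator: r = 0.5, an assumption. The plan adjusts for baseline by analysis of covariance but gives no correlation.
- True mediator effect d: the protocol gives none, so a range is shown. Its 0.42 refers to self-reported cognitive outcomes, not to a sleep measure.

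**Formulas.** With n per arm and outcome SD 1, the standard error of the first path is SE = √[(2/n)(1 − r²)].

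- n = 121: √[(2/121) × 0.75] = 0.111.
- n = 202: √[(2/202) × 0.75] = 0.086.

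Let μ = d/SE. The chance of passing is P = Φ(μ − 1.96) + Φ(−μ − 1.96). The mean first path among passing trials, relative to the truth, is 1 + [φ(1.96 − μ) − φ(1.96 + μ)] / (μP).

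**Results for one mediator, r = 0.5.**

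| True effect d | 121/arm: gate fails | 121/arm: inflation if passed | 202/arm: gate fails | 202/arm: inflation if passed |
|---|---|---|---|---|
| 0.2 | 56% | 50% | 36% | 25% |
| 0.3 | 23% | 15% | 6% | 4% |
| 0.4 | 5% | 3% | 0.4% | 0.2% |
| 0.5 | 0.6% | 0.4% | under 0.1% | under 0.1% |

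**Sensitivity to the baseline correlation.** With r = 0 and 121 per arm, SE = √(2/121) = 0.129. At d = 0.2, 0.3 and 0.5 the failure rates are 66%, 35% and 3%, and the inflation is 69%, 25% and 2%.

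**Does the inflation reach the indirect effect?** A simulation of the product of paths used 121 per arm, no baseline adjustment, ISI effect 1.0 SD, mediator correlation 0.5 and mediator-to-outcome slope 0.3 (all assumed except the 121). Without a gate, the mean estimate was 0.99 to 1.00 times the truth. Under the joint gate:

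- Sleep-efficiency effect 0.3 SD: the gate passed in 64% of runs. The sleep-efficiency indirect effect was 1.25 times the truth and the ISI indirect effect 1.04 times.
- Sleep-efficiency effect 0.6 SD: it passed in 99%, with ratios of 1.01 and 1.00.

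So the inflation of the first path carries over almost one for one to the same mediator's indirect effect, and spills over only slightly to the other. In the first case the joint gate also cancelled the ISI analysis in about 36% of runs (100 − 64), although an ISI effect of 1.0 SD alone would pass practically always.

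**The case against.** The best defence is that the condition follows the causal argument in the Background: treatment should improve sleep, and cognition should then improve through sleep. If treatment does not detectably move a mediator, the first link is unsupported, and the efficacy analysis of ISI and sleep efficiency would still report that. Requiring evidence on the first path is a familiar pre-specified step. The protocol also expects the gate to pass: "Online interventions have shown robust effects on insomnia severity and self-reported sleep parameters".

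Much of this stands. Three stronger readings are tempting, and the document does not support them.

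- *Both mediators must certainly be significant.* This is the literal sense, but the word *both* does not appear, and the slash notation permits a gate for each mediator. The defect is that the rule is unclear, not that the joint rule is established.
- *The surviving indirect effects will be materially inflated.* The direction follows from the estimator, but the size depends on an effect the protocol does not give. The 56% and 50% figures belong to an assumed 0.2 SD and to the full planned attrition. With less attrition or a larger effect they shrink quickly.
- *The trial will be unable to address its second aim.* A failed gate would leave the planned mediation models unrun, but the effects on the sleep measures would still be reported.

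The defence does not answer two points. A non-significant first path is not evidence that the path is absent, and the interval for the indirect effect already reflects a weak one. The gate therefore adds little while creating the ambiguity and the selection.

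**Conclusion.** The concern holds in a limited form. The plan makes an unconditionally stated aim depend on a significance test, gives no fallback, and leaves open whether the test is joint or per mediator. The lack of a fallback and the ambiguity do not depend on any effect size.

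The numerical harm does. It is appreciable for a true mediator effect of about 0.3 SD or less, small at 0.4 SD and negligible from 0.5 SD, given 121 per arm and a baseline correlation of 0.5. A lower correlation makes it worse and better retention makes it milder. If the effects on sleep are as robust as the protocol expects, the gate will nearly always pass and the bias will be trivial. The primary comparison, its error rate and the efficacy estimates are untouched. This is a cheap improvement to a secondary analysis, not a threat to the trial's main conclusion.

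**What to change.** Delete the if-then condition from the mediation paragraph. State instead that the indirect effect through ISI and the indirect effect through sleep efficiency will each be estimated in separate models for every stated cognitive outcome at week 24. Report each with its bootstrap interval and the residual direct effect, whatever the week-10 p-value of either mediator. Where treatment barely moves a mediator, the interval will show it.

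If the investigators prefer to keep a gate, the least they should do is state before the data are seen that it applies to each mediator separately, and label the resulting estimates as conditional on passing. That removes the cross-cancellation but not the selection.

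The cost is a change of wording and a few more models. The downside is that some reported indirect effects may have wide intervals.
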